# Protocol for a feasibility registry-based randomised controlled trial investigating a tailored follow-up service for stroke (A-LISTS)

**DOI:** 10.1186/s40814-024-01527-y

**Published:** 2024-07-30

**Keywords:** Stroke, Clinical trial protocol, Follow-up service, Clinical Quality Registry

## Abstract

**Background:**

Stroke affects long-term physical and cognitive function; many survivors report unmet health needs, such as pain or depression. A hospital-led follow-up service designed to address ongoing health problems may avoid unplanned readmissions and improve quality of life.

**Methods:**

This paper outlines the protocol for a registry-based, randomised controlled trial with allocation concealment of participants and outcome assessors. Based on an intention-to-treat analysis, we will evaluate the feasibility, acceptability, potential effectiveness and cost implications of a new tailored, codesigned, hospital-led follow-up service for people within 6–12 months of stroke. Participants (*n* = 100) from the Australian Stroke Clinical Registry who report extreme health problems on the EuroQol EQ-5D-3L survey between 90 and 180 days after stroke will be randomly assigned (1:1) to intervention (follow-up service) or control (usual care) groups. All participants will be independently assessed at baseline and 12–14-week post-randomisation. Primary outcomes for feasibility are the proportion of participants completing the trial and for intervention participants the proportion that received follow-up services. Acceptability is satisfaction of clinicians and participants involved in the intervention. Secondary outcomes include effectiveness: change in extreme health problems (EQ-5D-3L), unmet needs (Longer-term Unmet Needs questionnaire), unplanned presentations and hospital readmission, functional independence (modified Rankin Scale) and cost implications estimated from self-reported health service utilisation and productivity (e.g. workforce participation). To inform future research or implementation, the design contains a process evaluation including clinical protocol fidelity and an economic evaluation.

**Discussion:**

The results of this study will provide improved knowledge of service design and implementation barriers and facilitators and associated costs and resource implications to inform a future fully powered effectiveness trial of the intervention.

**Trial registration:**

ACTRN12622001015730pr.

**Supplementary Information:**

The online version contains supplementary material available at 10.1186/s40814-024-01527-y.

## Background

Stroke is a leading cause of global disease burden [1]. In addition to the immediate physical, cognitive and emotional injury impacts post-stroke, the long-term effects can be significant and life-altering. Approximately, 25% of people with stroke report their quality of life as equivalent to, or worse than, death [2]. Physical disability, loss of employment, social isolation, cognitive impairment, communication difficulties, anxiety and depression make resuming home and community activities difficult [3]. Furthermore, compared with hospital discharges to rehabilitation or aged care, people discharged directly home are at an increased risk of an unplanned readmission within 90 days (sub-hazard ratio, 1.44 [95% *CI*, 1.33–1.55]) [4]. Further, one in five people living with stroke have no support services in place after discharge from hospital [4].

Data from the Australian Stroke Clinical Registry (AuSCR) describe significant impacts on people with stroke or transient ischaemic attack (TIA) between 90 and 180 days after hospital admission [5, 6]. For example, health-related quality-of-life data (EQ-5D-3L, EuroQoL 5-dimensions 3-level version) [7] demonstrated that patients reported some or extreme problems with mobility (50%), self-care (30%), usual activities (58%), pain/discomfort (49%) and anxiety or depression (49%) [7]. To help mitigate these reported problems, efforts to better integrate care across hospital and primary care settings for chronic diseases such as stroke are required.

Evaluation from follow-up services in other countries is promising [8–10]. For example, a stroke nurse navigator programme in the United States reduced 30-day unplanned readmissions by 67.6% [10]. In addition, several authors of different studies have reported positive findings for follow-up services delivered from 30 to 90 days within the Australian context [11, 12]. In the study by Pugh et al., when compared with usual care, the nurse-led model of transitional care for neurology patients discharged from hospital produced cost savings, a positive return on investment, improved functional status and health-related quality of life [12]. In a separate feasibility study for the use of a modified World Stroke Organization post-stroke checklist in a rehabilitation setting, the authors reported improved communication with patients and timely referrals to appropriate clinical services [11]. Although these studies suggested that 60% of people living with stroke still had a least one health problem at 3-month follow-up [12], no studies have focused on providing follow-up support after 3 months.

More efficient and targeted approaches that include better communication between hospital specialist services and primary care providers are required for people living with stroke in Australia [13]. Furthermore, some stroke impacts may only become apparent post-discharge, and community-based services may lack the expertise to address stroke-related problems. To address this important gap in stroke care, we codesigned a registry-based, hospital-led tailored follow-up service with key stakeholders and people with lived experience as part of the AuSCR *LI*fe after *S*troke *T*ailored *S*upport (A-LISTS) study [14]. The follow-up service includes an intervention package that comprises a clinical protocol and procedure manual to be used by the site service coordinators (hereafter service coordinator/s) to tailor the support provided to the individuals with identified unmet need(s) [14]. The service coordinator is a nominated stroke clinician — nurse or allied health staff — who is trained in the procedures. The newly developed follow-up service intervention package was pilot tested in one urban hospital in Australia with six participants and then refined based on feedback from the service coordinator and participants to ensure it was ready to be used in a feasibility randomised controlled trial (RCT).

## Methods

### Research aims

The aim of the study is to assess the feasibility (i.e. acceptability and satisfaction of service coordinators and participants), potential clinical effectiveness, participant resource utilisation and cost implications of the tailored hospital-led follow-up service for chronic stroke compared with usual care (control).

### Study design

Multicentre, registry-based, trial with a prospective, parallel, randomised controlled, two group, single-blinded design (Fig. 1) with an intention-to-treat analysis. The RCT has been prospectively registered with Australian New Zealand Clinical Trials Registry (ACTRN12622001015730p, 20th July 2022).

**Fig. 1 Fig1:**
[figure not shown]
Overview of study design

Methods and results will be reported in compliance with the CONSORT 2010 statement, including the extension for randomised pilot and feasibility trials [15]. A process evaluation and an economic evaluation will be conducted concurrently to the main trial and will be reported using the relevant reporting guidelines (e.g. CHEERS checklist) [16]. The study database will be created via REDCap (Research Electronic Data Capture; a secure web based data management system) [17] and will be hosted on the Florey Institute of Neuroscience and Mental Health servers under the security and information technology infrastructure of the University of Melbourne, and will be protected as per industry standards.

### Study setting

Up to six eligible and interested hospitals from a variety of settings will be identified from the network of hospitals that participate in the AuSCR (*n* = 63 hospitals). Commencement dates will be staggered due to the timing of receiving hospital governance approvals, onboarding and training procedures. The AuSCR is a national clinical quality registry that collects prospective data on all patients from participating hospitals with a clinical diagnosis of stroke or TIA with the purpose of monitoring and improving stroke care in Australia [18]. The diagnosis is confirmed by the registrant when they complete a follow-up survey at 90–180 days. Within the AuSCR, data on demographics, clinical characteristics and evidence-based therapies provided to patients during the acute admission are collected by hospital staff. Registrants are then contacted by the AuSCR Office, initially by mail to complete a follow-up health outcome survey. Where there is no response, a short message service (SMS) and/or mail to the nominated next of kin is sent between 90 and 180 days post admission. The AuSCR Office attempts to obtain health outcomes from all registrants unless they request no follow-up, opt out of having their personal details stored on the registry, were registered on the AuSCR over 180 days post discharge, or were known to be deceased. At the 90–180 day follow-up, registrants provide information about their living situation and provide health-related quality of life (HRQoL) details using the EQ-5D-3L survey including the visual analogue scale (VAS) [19]. Functional independence is collected using the modified Rankin Scale (mRS) [20], and participants are also asked to indicate their willingness to be contacted for further research opportunities.

### Study population

#### Inclusion criteria

Participants are selected from the AuSCR registrants if they:Have indicated a willingness to be contacted for future research at 90–180 day follow-upAre aged ≥ 18 years with a confirmed diagnosis of strokeAre living in the community in a private residenceHave reported an extreme problem in at least one dimension of the EQ-5D-3L or have a score on the VAS ≤ 60 at 90–180 day follow-up [19]Are able to participate in English and provide informed consent (self-report or appropriate proxy can assist).

#### Exclusion criteria

AuSCR registrants with a TIA diagnosis will be excluded. Registrants in palliative care and/or a residential aged care facility will be excluded as they may be unlikely to survive to the end of study follow-up period (i.e. 12–14-week post-randomisation).

### Trial procedures

#### Registry-based participant recruitment procedure

Identification of eligible AuSCR registrants and recruitment will be undertaken by the data manager located at AuSCR Office in Melbourne, Victoria. Trained AuSCR team members will call potential participants to confirm eligibility. Consent will be obtained via mail (paper form) or email (e-consent; purpose designed in the REDCap database). Baseline assessments (including demographic and clinical data) will be completed by an AuSCR team member via telephone post consent. Figure 2 outlines the recruitment pathway. A screening log will be used to capture demographic information on consenting eligible registrants and those who are not, to enable reporting of response and participation rates.

**Fig. 2 Fig2:**
[figure not shown]
Summary of the recruitment and intervention pathway

#### Randomisation, allocation concealment and blinding procedure

Once consented, the trial participants will be randomly allocated 1:1 to the intervention group or control (usual care) group. Online randomisation will occur using REDCap [17], stratified by age (< 65, 65 + years) and sex (male, female) to ensure balance of age and sex between the two groups as these factors are associated with differences in HRQoL [21]. Participants and outcome assessors (AuSCR staff) will be blinded to the group allocation. Service coordinators delivering the intervention will be unaware of participants from their hospital randomised to the control group. To avoid unblinding to group allocation, the control group will not know which group they are in. As part of the study, some participants may be contacted by a member of staff from the hospital or service that treated them for their stroke.

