Clinical evaluation	Quality of life^b^	EQ-5D-3L (baseline: to verify responses from pre-trial is still current, and eligibility is still met for the service)	All participants in conjunction with blinded AuSCR follow-up team member		X		X	
	Disability/dependence^b^	mRS (baseline: to verify responses from pre-trial is still current, and eligibility is still met for the service) Communication and fatigue (yes/no and 5-point Likert scale, respectively)			X		X	
	Unmet needs	Longer-Term Unmet Needs for Stroke questionnaire [22]			X		X	
	Unplanned hospital readmissions, ED visits^b^	Survey tailored for A-LISTS trial			X		X	
	Serious adverse events^b^	Serious adverse events form specific for A-LISTS trial				X	X	
	Health service use diary for participants	Developed for trial to support recall; used as memory aid at the outcome assessment to respond to questions about current health services used	All participants			X		
Process evaluation	Satisfaction & experiences with service and study participation	Theory-informed survey and/or semi-structured interview/focus groups	Intervention participants				X	
	Satisfaction with service, including implementation features & intervention fidelity	Theory-informed survey and semi-structured focus groups [23, 24]	Service coordinator and clinicians					X
	Participation numbers, recommended actions, uptake of service coordinator recommendations	Template tailored for A-LISTS study; patient-level data will be aggregated	Service coordinator			X		
	Project documentation	Standard operating procedures, minutes, training documents, project notes	Project team, investigators	X	X	X	X	X
Economic evaluation	Current health services used, medications, costs^b^ Programme delivery costs	Resource use questionnaire developed for trial Research (financial) documents, invoices			X		X	

*Abbreviations*: *AuSCR* Australian Stroke Clinical Registry, *EQ-5D-3L* EuroQol 5-dimension 3-level survey; *mRS*, modified Rankin Scale

^a^Standard Australian Stroke Clinical Registry follow-up survey completed 90-180 days after admission

^b^indicates data will also be used for the economic evaluation

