### Treatment groups

#### Intervention

Participants in the intervention group will receive the tailored follow-up service implemented over 12 weeks. The service coordinator will be provided with a tailored patient referral report (including demographic and clinical data collected from the baseline assessment). The intervention follow-up service utilises clinicians’ clinical reasoning and experience to help participants navigate the hospital, community and primary care systems. This support may include linking participants to appropriate locally available services. All service coordinators will have a clinical background in stroke (e.g. stroke nurse, stroke allied health) and will receive 4–8 hours of training tailored to the hospital setup. The service coordinator will conduct an initial assessment with the participant (either in-person or via telehealth; participant’s choice) to ascertain existing service usage and how to assist the participant with their unmet needs. Through a collaborative and shared decision-making approach with the participant, the level of input required will be tailored to the participant’s needs. The service coordinator will then organise referrals as required and provide advice and education as necessary.

Following the initial consultation, there are six possible scenarios (Fig. 2). Only existing and available services or treatments will be offered in the trial. The intervention follow-up service will be tailored to the individual participant. It does not dictate how often or which clinicians or services will have ongoing engagement with participants over the 12-week intervention period. Participants will be asked for their permission to share information with their general practitioner (GP) including the purposively designed A-LISTS GP letter. Depending on the participant’s age, location, needs, priorities and healthcare network, we envisage that some participants may be referred to services such as allied health services (e.g. physiotherapy, occupational therapy), community rehabilitation programmes and state-funded community health programmes (e.g. chronic disease management plan [31]). The service coordinator may also liaise with the National Disability Insurance Scheme [32], My Aged Care [33] and other stroke resources (e.g. Stroke Foundation services and information) to help participants navigate the system and provide education.

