#### Satisfaction survey

All participants will be invited to complete an electronic/paper satisfaction survey (including open and closed questions) at the 12–14-week post-randomisation outcome assessment. Information on satisfaction and experience with the care received in the community will be obtained, with specific questions related to the service coordinator and follow-up service also included for those in the intervention group. The service coordinator (and any other clinicians involved in the initial consultation) will also be invited to complete a survey exploring their experience of implementing and delivering the follow-up service.

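### Participant blinding is claimed but is not a property of this design, and assessor blinding is exposed to disclosure at the 12–14-week assessment

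*Protocol article*

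**What the plan says.** The article describes masking in three places, in three ways.

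- Abstract, Methods: "allocation concealment of participants and outcome assessors".
- Study design: "two group, single-blinded design".
- Randomisation, allocation concealment and blinding procedure: "Participants and outcome assessors (AuSCR staff) will be blinded to the group allocation".

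The last section then gives the means of masking participants: "To avoid unblinding to group allocation, the control group will not know which group they are in". It adds that "some participants may be contacted by a member of staff from the hospital or service that treated them for their stroke".

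Under Intervention, "The service coordinator will conduct an initial assessment with the participant", in person or by telehealth. Referrals, advice and education follow as needed over 12 weeks, and permission is sought to share information with the GP, including a trial-specific letter. Controls receive usual care, and no sham or attention contact is described for them.

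Table 2 has the EQ-5D-3L completed at 12–14 weeks by the participant together with a blinded registry team member. That entry appears to carry down to mRS, LUNS, readmissions and serious adverse events. Both arms keep a diary of contacts and referrals, which Table 2 says is "used as memory aid at the outcome assessment to respond to questions about current health services used". The satisfaction survey falls at the same time point, "with specific questions related to the service coordinator and follow-up service also included for those in the intervention group".

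**The concern.** A reader cannot tell from the article who is masked. One party is masked under the study design label and two under the randomisation section. The abstract uses a term that belongs to the period before assignment, not to masking afterwards.

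The participant claim matters most. EQ-5D-3L, VAS and LUNS are the participant's own ratings. If participants know they received a service, their ratings can reflect that knowledge, however well the assessor is masked. A report that repeats the participant-blinding claim would overstate the protection these comparisons have.

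The assessor claim matters for the mRS, for any probing during the interview, and for self-reported presentations and admissions. The assessment that records the health outcomes also asks about service use, so allocation could surface in the same conversation.

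The outcomes concerned are secondary, but the plan relies on them. They enter adjusted between-group models with confidence intervals meant to inform discussion of likely treatment effects. They supply the progression criterion that at least 30% improve from baseline. The Discussion also says they will support effect sizes for planning a fully powered trial.

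**Working it through.** No arithmetic applies. The article gives no unblinding rate and no assumed effect, so the check is to set the statements side by side.

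**Step 1: are the labels compatible?** Study design names one masked party by implication, and the randomisation section names two. The abstract applies allocation concealment to both. A full protocol or analysis plan that is not shown cannot make these three statements agree; the wording has to change.

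**Step 2: can participants be blinded?** The stated means covers one arm.

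| Feature | Intervention | Control |
|---|---|---|
| Told or left unaware | No means of masking stated | Will not know their group |
| Contact with a service coordinator | Initial assessment, then tailored support | None described during follow-up |
| Trial-specific GP letter | Yes, with permission | None described |
| Survey items about the coordinator and service | Yes | No |
| Sham or attention contact | Not applicable | None described |

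An intervention participant meets a coordinator under a trial they consented to, and is later asked about that coordinator and the service. At most, such a participant has not been formally told the name of the arm. That is weaker than being blinded to allocation.

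**Step 3: can the assessor stay blinded?** The health outcomes and the service-use questions belong to the same 12–14-week assessment. The diary records contacts and referrals with dates and reasons, and a full answer from an intervention participant could name the coordinator. This is a route to disclosure, not evidence that it happens:

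- both arms keep the diary, and it is the participant's memory aid;
- controls also use existing services, so a reported contact does not in itself identify the arm;
- the satisfaction survey is electronic or on paper, and nothing shows that it passes through the assessor;
- the article does not give the order of questions.

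**Step 4: which results depend on it?** Trial completion and attendance at the service are primary and descriptive, and do not rest on blinded ratings. The self-reported health outcomes do depend on it. Even a perfectly masked assessor would leave EQ-5D-3L, VAS and LUNS open to expectation effects, because the participant is the rater.

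**The case against.** The strongest reply is that the assessor half rests on silence. A journal article condenses the full protocol. Question order, interviewer scripts and checks on masking usually sit in operating procedures, which Table 2 lists among the project documents and which are not shown. This stands. A reader might infer that nothing prevents disclosure and that assessor blinding therefore fails; the document does not support that.

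A second reply is that participant information was deliberately limited: hospital contact is presented as something some participants may receive, and the consent material is not shown. This supports the masking of controls. It does not make someone who has had a coordinator assessment blind to having received it.

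Third, a reader might treat the adherence criterion of more than 70% attending the initial consultation as a guide to how often allocation is revealed. It is a progression threshold for attendance and says nothing about disclosure to the assessor.

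Fourth, not every outcome rests solely on self-report to the assessor. Medical records may be audited to verify resource-use data, and serious adverse events draw on hospital records where possible. That stands too, so the expectation-bias point is confined here to EQ-5D-3L, VAS and LUNS.

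Finally, the outcomes are secondary, the article acknowledges the limits of effectiveness comparisons in feasibility trials, and the analysing statistician is blinded. These points reduce the stakes. A blinded analyst, however, does not correct ratings given by an unblinded participant.

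**Conclusion.** The claim that participants are blinded is not supported by the design described, and the three accounts of masking must be reconciled. This conclusion rests only on printed text and does not depend on unseen procedures.

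Assessor blinding is plausible but exposed. Whether it is protected depends on the order of questions and on how the survey is handled, neither of which the article states.

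The size and direction of any bias cannot be derived. The consequence is one of interpretation: between-group differences in EQ-5D-3L, VAS and LUNS, the 30% improvement criterion, and effect sizes carried into a definitive trial are open to expectation bias and should not be presented as protected by participant blinding. The primary outcomes of completion and attendance are not undermined. The point deserves correction because the claim will be repeated in the trial report and the remedy is inexpensive.

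**What to change.** 1. **Wording.** In the abstract, Study design and the randomisation section, use one description: outcome-assessor blinded, with control participants not told their allocation. Remove the statement that participants are blinded, and keep allocation concealment for the period before assignment.
2. **Interpretation.** State that the self-reported EQ-5D-3L, VAS and LUNS comparisons are open to expectation bias, and carry that caveat into the progression decision and any effect-size planning.
3. **Conduct, unless operating procedures already provide for it.** Record EQ-5D-3L and VAS, mRS and LUNS before any service-use question. Keep the arm-specific satisfaction items, electronic or paper, away from the assessor. Log whether allocation was revealed to the assessor, and when.

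The changes are to wording, form order and a short log; no extra visits are needed. There are two costs. The blinding claim becomes weaker. And since 50 of up to 100 participants had been randomised by 1 May 2024, a new order of administration would be a mid-trial change: it must be dated and documented, and earlier and later assessments may not be fully comparable. Reordering protects the assessor's masking only; it cannot remove expectation effects in participants' own ratings, which is why items 1 and 2 are needed in any case.
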